## Abstract

**Background:**

Communication impairment is a frequent consequence of stroke. Patients who cannot articulate their needs respond with frustration and agitation, resulting in poor optimization of post-stroke functions. A key component of patient-centred care is the ability of staff to communicate in a way that allows them to understand the patient’s needs. We developed a patient-centred communication intervention targeting registered and unregulated nursing staff caring for complex continuing care patients with communication impairments post stroke. Research objectives include 1) examining the effects of the intervention on patients’ quality of life, depression, satisfaction with care, and agitation; and (2) examining the extent to which the intervention improves staff’s attitudes and knowledge in caring for patients with communication impairments. The intervention builds on a previous pilot study.

**Methods/design:**

A quasi-experimental repeated measures non-equivalent control group design in a complex continuing care facility is being used. Patients with a communication impairment post-stroke admitted to the facility are eligible to participate. All staff nurses are eligible. Baseline data are collected from staff and patients. Follow-up will occur at 1 and 3 months post-intervention. Subject recruitment and data collection from 60 patients and 30 staff will take approximately 36 months. The Patient-Centred Communication Intervention consists of three components: (1) development of an individualized patient communication care plan; (2) a one-day workshop focused on communication and behavioural management strategies for nursing staff; and (3) a staff support system. The intervention takes comprehensive patient assessments into account to inform the development of communication and behavioural strategies specifically tailored to each patient.

**Discussion:**

The Patient-Centred Communication Intervention will provide staff with strategies to facilitate interactions with patients and to minimize agitation associated with considerable stress. The improvement of these interactions will lead to a reduction of agitation, which has the additional significance of increasing patients’ well-being, quality of life, and satisfaction with care.

**Trial registration:**

ClinicalTrials.gov Identifier NCT01654029

## Background

Whereas stroke is a leading cause of death in the United States and Canada, survival estimates are 75% - 85% in both countries [1,2]. About 10% of patients with disability post-stroke live in institutions [3]. More than 300,000 stroke survivors in Canada typically live with substantial and lasting physical and neuro-cognitive deficits [4,5], with 25-40% of them presenting with aphasia, the inability to produce or understand language [6]. These patients often are admitted to a long term care (LTC) facility because of their neurological disorders [7]. Up to 50% of LTC patients have speech and communication impairments [8]. When patients can neither articulate their needs nor be understood following a stroke, depression, agitation and behavioural symptoms often ensue [9-12].

Traditionally, nursing staff have treated behavioural symptoms exhibited by patients with stroke with restrictive interventions such as physical, environmental or chemical restraints [13], which are regarded as a major threat to patient care quality [14]. Additionally, caring for patients with behavioural symptoms contributes to staff burnout, which eventually leads to staff turnover, and negatively influences care quality [15]. Patient-centred care has emerged as a crucial underlying principle for the delivery of quality care in LTC facilities [16]. A key component of patient-centred care is the ability of staff to communicate in such a way that allows them to understand the patient’s needs. Research indicates that the occurrence of behavioural symptoms can be mitigated by the way nursing staff communicate with patients [17]. Therefore, enhancement of nursing staff’s communication strategies has been identified as a priority for LTC environments [18] and for maintaining patients’ quality of life [19]. However, two significant limitations of patient-centred care exist. First, the responsibility for ensuring the patient’s best care falls upon the nursing staff (both registered and unregulated care providers). However, many nursing staff lack the requisite specialized skills and abilities to effectively communicate with patients who have communication impairments and hence have difficulties understanding patients’ needs [8,20]. Providing assistance with personal care activities such as dressing, toileting and transferring requires frequent interactions between patients and nursing staff and if these interactions are compromised by communication breakdown and subsequent agitation, personal care interactions are disrupted and quality of care is undermined [19]. The end result is that the patient’s post-stroke functions and well-being are not optimized. Second, a recent systematic review of communication studies identified an absence of evidence-based interventions designed to enhance communication with patients with stroke living in LTC [21]. Improved staff communication with these patients is the basis for assessing patients’ needs and for providing patient-centered care.

Methodological and theoretical limitations across the studies that evaluated communication- focused interventions have left significant gaps in our understanding of how to effectively improve LTC staff’s communication skills. Approaches to communication training have been based on general recommended linguistic strategies [20,22]. Only one study had individualized tailored communication training [23]. Conversely, evidence is accumulating that communication enhancement strategies should be based on individualized patients’ remaining communication abilities [24,25]. Provision of effective and responsive care demands a focus on both communication and behavioural management strategies. How staff communicate with patients when a behavioural symptom occurs can influence patients’ behavioural symptoms [10,17].

To address some of these limitations, [name] and colleagues [26] developed and pilot-tested a patient-centred communication intervention (PCCI) targeting nursing staff caring for patients with communication impairments post-stroke. The PCCI involved training by a Speech-Language Pathologist (SLP) to 18 nurses on 1 LTC unit on communication impairments and supportive conversation strategies. The SLP also developed individualized patient communication care plans based on initial assessments. The recent pilot work referred to as PCCI enhances quality of life, reduces agitation in patients and in turn creates more cooperative and less stressful caregiving situations for nurses [26]. The pilot study provided evidence to support the feasibility of a larger scale study to examine the efficacy of the PCCI, to determine its long-term effects, to test the intervention in new sites, and to determine its effects on a range of outcomes in a large sample of patients.

### Specific aims

This study implements the PCCI in Complex Continuing Care (CCC) with the objective to educate, train and support nursing staff in communicating effectively with patients who have communication impairments as a result of a stroke. The specific objectives include 1) to determine the effects of the PCCI on improved patient quality of life (communication and psychosocial domains), satisfaction with care, and agitation, at 1 and 3 months post-intervention; and 2) to examine the extent to which the PCCI improves nursing staff’s attitudes and knowledge about caring for patients with communication impairments at 1 and 3 months post-intervention.

## Methods/design

A quasi-experimental repeated measures non-equivalent control group design guides this study. In this design, control subjects from two units in one facility were enrolled and followed for up to three months, dependent on when they were discharged. Once the control subjects were accrued, staff from the facility were trained in the PCCI model. Currently the intervention cohort is being enrolled and followed.

Outcome data pertaining to the variables of interest are obtained from the patient participants in the control and experimental units at 3 different time points: 1) baseline, prior to delivering the intervention; 2) post-test 1, within 4 weeks after completion of the intervention; and 3) post-test 2, 3-months after completion of the intervention. Outcome data pertaining to the nursing staff are obtained at baseline and again at post-test 2 or prior to the patient’s discharge. Ethics approval was received from the Toronto Rehabilitation Institute Research Ethics Board #09-009 and from the research facility ethics board #2010-002-1002.

### Setting and sample

In order to accrue the required sample size, one of the largest CCC facilities in the Greater Toronto Area, Ontario, Canada, is participating in this study. In Ontario, CCC provides medically complex and specialized services over extended periods of time. Clients are usually admitted to a CCC unit following an acute care episode and are generally younger and have higher acuity needs than clients found in long-term care settings. Most clients will remain on these CCC units for an extended length of stay. CCC is often used interchangeably with “extended care” or “chronic care” [27]. The selected facility has approximately 300 patients and has 2 units with patients who have suffered a stroke. One unit has residents who stay for up to 1 month and the other unit has a length of stay closer to 3 months as patients have different levels of acuity, which will be accounted for in the analysis.

The sample consists of nursing staff (health care aides/personal support workers, registered practical nurses, registered nurses) and patients from the selected units. Eligibility criteria for staff include 1) are directly involved in providing care; 2) work full or part-time; and 3) consent to participate in the study. All staff members employed in the selected institutions are required to speak, read and write in English, and have the basic skills and knowledge to care for stroke patients.

Patients are invited to participate if they have been identified by the staff as having difficulties communicating. Specific inclusion criteria are 1) confirmed diagnosis of stroke, related to a cerebral infarct, as reported in the patient’s medical chart; and 2) English as the mother tongue or ability to sufficiently speak and understand English before the stroke as assessed by the staff on the unit and/or as reported by the family. The exclusion criterion ensures that patients can reliably self-report; it includes severe receptive aphasia (i.e. global aphasia and severe Wernicke’s aphasia). The facility speech-language pathologists assess newly admitted patients for their potential appropriateness for the study. A potential subject’s nurse will obtain permission from the patient and/or family to allow the research assistant to explain the study and consent process. If a participant is deemed unable to consent, an authorized representative will provide informed consent with the assent of the patient. A copy of the signed informed consent will be given to the participant.

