### Intervention

The intervention consists of three components: (1) development of individualized communication care plans; (2) nursing staff attendance at a workshop focused on communication and behavioural management strategies; and (3) implementation of a staff support system. The intervention will take 2 months to implement.

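### Post-tests in both cohorts are timed from completion of an intervention that controls never receive, and the short-stay unit cannot supply 3-month scores

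*Protocol article*

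**What the plan says.** Methods/design in the protocol article sets one visit schedule for "patient participants in the control and experimental units at 3 different time points". The first is "baseline, prior to delivering the intervention". The other two are "post-test 1, within 4 weeks after completion of the intervention" and "post-test 2, 3-months after completion of the intervention".

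The same section says that control patients "were enrolled and followed for up to three months, dependent on when they were discharged", and that staff training began only once the controls had been accrued. For staff outcomes it allows the last measurement to be taken before the patient's discharge. It gives no such rule for patient outcomes.

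The Intervention section says "The intervention will take 2 months to implement". Setting and sample says "One unit has residents who stay for up to 1 month and the other unit has a length of stay closer to 3 months", and adds that the analysis will allow for this difference.

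Specific aims makes effects at both 1 and 3 months an objective. Sample size places the patient primary outcome at 1 month and assumes three repeated measures per patient. Objective #1 gives most weight to contrasts showing when change occurs and whether it lasts.

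**The concern.** A visit schedule counted from the end of the intervention needs an end date for every patient. Controls have none, and the article gives them no substitute. Without a common origin, the two cohorts may be measured at different times after baseline. That matters in a non-randomised comparison of sequential cohorts, most of whom come from an acute episode, because time since baseline may itself bring change.

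Separately, the stated lengths of stay do not fit a 3-month visit on one of the two units. At stake is the claim that any effect is maintained at 3 months. For the short-stay unit that claim would come from the model and not from observed scores.

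**Working it through.** **Inputs.** Stay up to 1 month or about 3 months (Setting and sample). Intervention 2 months (Intervention). Post-test 1 at 0 to 4 weeks and post-test 2 at 3 months after completion; control follow-up at most 3 months, ending at discharge (Methods/design). Effect 3.8, SD 5.0, intra-class correlation 0.40, three measures, alpha 0.05, N = 44 for 90% power, 60 planned (Sample size).

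**Timing, if the 2 months are per patient**
- Post-test 1: 2 months to 2 months + 4 weeks, so about 2 to 3 months after baseline.
- Post-test 2: 2 + 3 = 5 months after baseline.
- Controls: at most 3 months. The cohorts then differ by at least 5 − 3 = 2 months at post-test 2.
- A stay of up to 1 month ends before post-test 1. A stay of about 3 months can reach post-test 1 but not post-test 2.
- No control date for post-test 1 is given, so the gap at that visit cannot be calculated.

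**Timing, if the 2 months are a facility roll-out**
- Completion is one calendar date. It cannot time visits for patients enrolled afterwards, and Trial status shows the intervention cohort still accruing.
- If visits are taken instead at about 1 and 3 months from each patient's entry, the cohorts can be aligned. A stay of up to 1 month still ends well before the 3-month visit.

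The missing 3-month scores on the short-stay unit therefore do not depend on the reading. They depend only on the stated stays and on there being no follow-up after discharge.

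**Effect on the stated power.** The plan's figure comes from a two-group comparison with the variance multiplied by f = [1 + (m − 1) × 0.40] / m, where m is the number of measures, and standardised effect d = 3.8/5.0 = 0.76:

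Total N = 4 × f × [(1.960 + 1.282)/0.76]²

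| Measures per patient | f | Total N before rounding | N for 90% power (equal groups) | Power with 60 |
|---|---|---|---|---|
| 3 | 0.60 | 43.66 | 44 (the plan's figure) | 96.7% |
| 2 | 0.70 | 50.94 | 52 | 94.0% |

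Losing the third measure in every patient raises the requirement from 44 to 52, still within the planned 60.

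The loss is larger only if short-stay patients miss post-test 1 as well. The article does not give the split between units. With assumed short-stay shares of 25%, 50% and 75%, 30 per cohort becomes 22.5, 15 and 7.5, and power becomes 91%, 77% and 48%, even crediting three measures to everyone who remains.

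**The case against.** The facility-wide reading is the more likely one. The workshop and the three weeks of weekly support act on staff, consenting nurses had already attended the workshop, and patients were still being enrolled. Only the care plan and bedside kit are delivered per patient. Visits at about 1 and 3 months from entry would also fit Specific aims and the 3-month limit on control follow-up. This stands. A reader might infer that the primary comparison is confounded by a gap of up to 2 months at each post-test. The text does not establish that: it needs the less likely reading, and at post-test 1 it also needs a control date that the article does not state.

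A reader might also infer that the study is underpowered. With 10, 15 or 20 longer-stay patients per cohort (assumed), a baseline-adjusted comparison of 3.8 points at 3 months has 42%, 59% or 72% power (noncentral t, variance factor 1 − 0.40² = 0.84). These figures contradict nothing in the plan, which claims power only for the 1-month outcome.

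Missing 3-month scores affect both cohorts, since controls came from both units, and no difference in discharge between cohorts is shown. A hierarchical model can use incomplete series if scores are missing at random, and its exact terms may properly be left to an analysis plan. That also stands. But a unit or length-of-stay covariate adjusts scores that exist. Where a whole unit has none at 3 months, the effect there is extrapolated whatever covariate is added.

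**Conclusion.** The concern holds as a should-fix point. The stated timing rule cannot be applied to controls, and the 2-month duration is not tied to either the patient or the facility. Per patient, the cohorts differ by at least about 2 months at post-test 2 and short-stay patients miss post-test 1. Facility-wide, the rule cannot time visits for later enrolments. On both readings the short-stay unit has no 3-month scores, provided that stays are as stated and patients are not followed after discharge.

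The main harm is to the 3-month maintenance conclusion. The sample size of 44 reproduces, and power for the primary outcome is little affected if post-test 1 is obtained.

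**What to change.** Reconcile Methods/design, Setting and sample, and Intervention as follows.

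- State whether the 2 months are per patient or facility-wide.
- Define post-test 1 and post-test 2 in both cohorts from one origin that both have, the patient's own baseline, with the same windows as were used for the completed controls.
- Use the recorded assessment day in the model for both cohorts.
- Define the 3-month contrast for the longer-stay unit only, report the number observed at 3 months in each cohort, and make no 3-month claim for the short-stay unit.
- Use patient scores taken just before discharge only if the controls also have them. All 30 controls are complete, so adding such an assessment for intervention patients alone would create a new imbalance.

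The intervention is unchanged. The cost is revised wording on timing and analysis, retrieval of the controls' assessment dates, and a narrower 3-month conclusion. If the 2 months prove to be per patient, a visit set at 1 month from baseline would fall before delivery is complete, and the meaning of post-test 1 must then be stated accordingly.

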### Intervention

The intervention consists of three components: (1) development of individualized communication care plans; (2) nursing staff attendance at a workshop focused on communication and behavioural management strategies; and (3) implementation of a staff support system. The intervention will take 2 months to implement.

#### Workshop

All staff nurses who consent to participate in the study have attended a one day workshop taught by two of the investigators. The workshop covered content on communication and behavioural management and focused on refining the communication plans.

1. Communication management: Nursing staff are trained to use communication strategies that promote the patient’s ability to communicate, and acknowledge and reveal the patient’s competence. The strategies include an application of the ‘Supported Conversation for Adults with Aphasia’ training program [28] developed by staff at the Aphasia Institute. This approach is based on the idea that the undamaged cognitive competence of individuals with communication disorders can be revealed through a trained conversation partner’s skill. Conversation partners, in this case nursing staff, are trained to acknowledge the patient’s competence using strategies such as natural adult talk and showing sensitivity to the person and context. They are also shown how to reveal patients’ competence by using strategies to ensure the patient understands what has been said and has a means of responding, and by verifying that this process has occurred. Nonverbal techniques that are used to acknowledge and reveal competence include gestures, writing, drawing, and using pictures and other resources. An adult learning approach was used to train nurses how to apply these strategies in practice [28-30].

2. Behaviour management: This component involves the use of the REAP (Relate well, Environmental manipulation, Abilities focused care and Personhood) model of practice [31]. The REAP model of care was conceptualized by the PI and has been used in other research with older adults. Staff nurses are taught that all behaviours have meaning, often related not to pathology but to unmet needs (e.g. physical, psychological/emotional, social, environmental) [32]. In other words, patients are exhibiting ‘responsive behaviours;’ that is, they are responding to such frustrations as discomfort, boredom, or loud sounds. Staff are encouraged to use the REAP model to determine the patient’s unmet needs and respond according to their assessment of these needs [31-37]. These strategies are also listed in the communication care plan. Four principles underlie the model:

i. Staff’s ability to relate well is an essential component of nursing staff-patient interactions [33,34]. Staff nurses are taught techniques to compensate for their patients’ impairments by using strategies found to be effective when patients are agitated such as calm voice, gentle touch, and calm approach.

ii. Environment-person theory[35] argues for the need for synergy between person and environment. The environment must be modified and changed to accommodate the person’s changing needs and preferences. For example, environmental noise should be reduced when communicating with a patient who is hearing impaired [36,37].

iii. Abilities focused care[37] involves staff focusing on patients’ retained abilities. The ability of persons with stroke to communicate is influenced by their spatial orientation, their hearing and vision, and their level of communication impairment. Staff nurses are informed by the SLP of the patient’s communication abilities and are taught to compensate where necessary.

iv. Personhood[38] refers to knowing the person, becoming familiar with the individual, and gaining knowledge of the person’s life. When providing care to patients, knowing what interests them helps to limit the patient’s behavioural symptoms [39]. Topics of interest (i.e., hobbies, families, etc.) for conversations that will engage the patient in meaningful interactions are obtained from the patient and family by the facility SLP and nursing staff.

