### Statistical analysis

#### Sample size

The primary outcome for the patients is an improvement in the communication domain of the SAQOL (SAQOL-com) from pre- to post-test at 1 month. In our pilot study, the mean SAQOL-com score increased 3.8 units to 21.0 from a baseline score of 17.2 [26]. The baseline standard deviation was 5.0. This provides a Cohen’s standardized effect size of 0.76. A sample size of 44 is estimated to have 90% power to detect this effect using a repeated measures hierarchical regression analysis with an intra-class correlation of 0.40 among the three repeated measures and for an alpha of 0.05 [55].

The primary outcome for the staff is an improvement in the score from pre- to post-test in attitudes related to communicating with patients who have communication impairments (CIQ). In the pilot study, the improvement was 2.4 with a standard deviation of 4.1 providing a Cohen’s standardized effect size of 0.58. A sample size of 55 is estimated to have 80% power to detect this effect using a repeated measures hierarchical regression analysis with an intra-class correlation of 0.40 among the three repeated measures for an alpha of 0.05 [55]. We plan to recruit 60 patients: 30 in the control group and 30 in the intervention group. Each patient assessment will include a nurse-patient interaction; therefore, the subjects will be recruited as nurse-patient dyads.

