#### Objective #2

The second objective evaluates the effects of the PCCI on staff’s attitudes and knowledge about caring for patients with communication impairments due to stroke. The same approach to analysis will be used to assess the effects of the PCCI on staff experiences as was used to assess the effects of the PCCI on patient quality of life. Staff attitudes and knowledge of care are now the outcomes measured at each time point and will be analyzed as (Level 1) repeated measures nested within (Level 2) patients using the hierarchical regression methods described in the previous paragraph.

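### The staff sample size of 55 assumes two independent groups of nurses, but the design has one workforce of 25–30 nurses, all trained, with no separate or concurrent untrained group

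*Protocol article*

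**What the plan says.** **Sizing.** For the CIQ, the Sample size section says that in the pilot "the improvement was 2.4 with a standard deviation of 4.1 providing a Cohen’s standardized effect size of 0.58". It then states: "A sample size of 55 is estimated to have 80% power to detect this effect using a repeated measures hierarchical regression analysis". The calculation assumes three measures per subject, ICC 0.40 and alpha 0.05. For patients, the parallel sentence reads: "A sample size of 44 is estimated to have 90% power to detect this effect". Allocation is given for patients only: "We plan to recruit 60 patients: 30 in the control group and 30 in the intervention group". The same section adds that recruitment is by nurse-patient dyad.

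**Analysis.** Objective #2 says: "The same approach to analysis will be used to assess the effects of the PCCI on staff experiences" as for patient quality of life. It places staff scores at Level 1 with patients at Level 2. Under Objective #1, the PCCI effect is the fixed effect of main interest and staff enter as a crossed random effect.

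**Who is trained, and when.** Methods/design: "Once the control subjects were accrued, staff from the facility were trained in the PCCI model". Workshop: "All staff nurses who consent to participate in the study have attended a one day workshop taught by two of the investigators".

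**How many nurses, measured how often.** The Abstract plans 30 staff, and Trial status reports 25 who have agreed and completed questionnaires. Methods/design gives two staff occasions: baseline, and post-test 2 or before the patient's discharge. The staff sizing uses three measures, and Specific aims names 1 and 3 months.

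**The concern.** Patients form two distinct cohorts, enrolled one after the other, so a cohort effect is a treatment contrast for them. Nurses do not. One workforce on the same two units serves both cohorts, and all consenting members are trained between them. With 60 dyads and 25–30 nurses, each nurse serves on average 60/30 = 2 to 60/25 = 2.4 dyads. A nurse paired with one control and one intervention patient would have scores under both cohort labels, so the patient's cohort does not define a staff treatment group.

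Two things are at stake for the staff primary outcome. The stated 80% power belongs to a comparison that the design does not contain. And a PCCI effect on staff, reported as if from a controlled comparison, would carry more causal weight than a contrast of largely the same nurses across two calendar periods can bear.

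**Working it through.** **Inputs (all from the protocol article).** Staff effect 2.4, SD 4.1, power 80%; patient effect size 0.76, power 90%; ICC 0.40; three measures; alpha 0.05. Sidedness is not stated. Two-sided is assumed, and it reproduces both stated figures.

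**Step 1: reproduce the stated sizes.** For two equal independent groups compared on the mean of m equicorrelated measures:

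total N = 4 (z₀.₉₇₅ + z_power)² / d² × [1 + (m − 1)ρ]/m

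With m = 3 and ρ = 0.40 the last factor is (1 + 0.80)/3 = 0.60.

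- Staff, d = 2.4/4.1 = 0.585: 4 × (1.96 + 0.84)² / 0.585² = 91.62, and 91.62 × 0.60 = 54.97, the stated 55. Power at 27.5 per group is 80.0%. With d rounded to 0.58 the total is 56.0.
- Patients, d = 0.76: 72.77 × 0.60 = 43.66, the stated 44. Power at 22 per group is 90.2%.

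One formula gives both figures. Other two-group variants for staff (one or two measures, change score, ANCOVA) give about 49 to 112. One-group pre-post variants give about 21 to 28. None gives 55.

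**Step 2: apply that formula to the nurses available.** Suppose 25 or 30 distinct nurses were split equally into two groups. The SD of the three-measure mean is 4.1 × √0.60 = 3.18.

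- 15 per group: SE = 3.18 × √(2/15) = 1.16; 2.4/1.16 − 1.96 = 0.11; power 54%.
- 12.5 per group: SE = 3.18 × √(2/12.5) = 1.27; 2.4/1.27 − 1.96 = −0.07; power 47%.
- With the two occasions in Methods/design, the factor becomes (1 + 0.40)/2 = 0.70 and power falls to 48% and 42%.

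**Step 3: size the comparison the design can support.** For one group of nurses, post versus pre, N = (z₀.₉₇₅ + z₀.₈₀)² × (SD of change)² / 2.4². The article does not say whether 4.1 is the SD of change or of a score. In the score reading, the SD of change is 4.1 × √[2(1 − 0.40)] = 4.49.

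| Reading of 4.1 | N for 80% (normal approx.) | Power, 25 nurses | Power, 30 nurses |
|---|---|---|---|
| SD of change | 22.9, so 23 | 80% | 87% |
| SD of a score, ICC 0.40 | 27.5, so 28 | 73% | 81% |

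The powers use the noncentral t. That 27.5 is also the per-group figure in Step 1 is a coincidence of the factors: 2 × 0.60 = 2(1 − 0.40).

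**Step 4: why an occasion term matters.** In a plain pre-post test with no control-phase information, retest gain or drift adds directly to the estimated effect. As an illustration with assumed values, 30 nurses and no true effect, a drift of 0.5 points is declared significant 9–10% of the time, and 1.0 point 22–25%, across the two SD readings.

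**The case against.** The strongest reply is that the design openly declares a sequential, non-equivalent control. Training came after control accrual and subjects are recruited as dyads, so control-phase dyads involve nurses not yet trained. If their CIQ scores were taken, a contrast of control-phase with intervention-phase change could remove at least part of the retest gain and steady drift. That stands. A reader might infer that staff have no untrained comparator at all, or that any drift must count as PCCI effect. The document supports neither. It supports only the absence of a separate or concurrent untrained group.

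A reader might also infer that the analysis throws away the within-nurse pairing. That does not follow: the staff primary outcome is worded as a pre- to post-test improvement, and Objective #1 gives staff a crossed random effect, which would link a nurse's scores across patients. The two-independent-group assumption is demonstrated for the sizing. For the analysis, the problem is the carried-over cohort effect and the patient-level nesting.

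A third reply is that 60 dyads exceed 55; 30 per group in the formula gives 83% power. But it treats 60 dyads as 60 independent nurses, which 25–30 nurses cannot supply.

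Finally, exact model coding may be left to an analysis plan. But the article itself states the 55, the 80%, the nesting and the carry-over, and these conflict with its own account of who is trained and how many nurses there are.

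**Conclusion.** The point holds in this form: the staff size of 55 is a two-independent-group, three-measure figure, while the design has one workforce of 25–30 nurses, all trained after control accrual and measured on two occasions. Under the article's own formula the power is about 47–54%, not 80%. This assumes two-sided testing, ICC 0.40, three measures and an equal split of distinct nurses. A lower figure of 25–29% arises if such halves are compared on change scores, but that method does not reproduce 55 and should not be attributed to the plan.

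The drift figures in Step 4 describe an uncontrolled pre-post test, which the article does not specify. They show the risk if that test became the fallback, not the error rate of the planned analysis.

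The staff question is not underpowered in every form. A within-nurse comparison of 30 nurses reaches 81–87%, and of 25 nurses 73–80%. What the design cannot provide is a staff effect set against concurrent untrained nurses.

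**What to change.** - **Sample size section.** Restate the staff sizing as a within-nurse post- versus pre-workshop comparison. Say whether 4.1 is the SD of change (about 23 nurses for 80% power) or of a score (about 28 with ICC 0.40), and give the power for the 25–30 nurses expected. These figures are for the simple paired comparison; estimating an occasion term as well will cost some precision. Reconcile the three measures here with the two occasions in Methods/design and the 1- and 3-month points in Specific aims.
- **Objective #2.** Make the nurse the Level 2 unit for CIQ and PICS. Replace the patient-cohort effect with an indicator for whether that nurse had been trained when the score was taken. Where control-phase staff scores exist, add an occasion (repeat-completion) term so that retest gain is not loaded onto training. Where none exist, report a before-after change.
- **Conclusion.** In either case, say that Objective 2 has no concurrent untrained staff control.

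The change is mainly one of wording and model specification. It weakens the causal claim for staff outcomes. Its feasibility rests on whether CIQ and PICS were collected before training and can be dated against the workshop, which the article does not state. Nurses without a pre-training score would contribute little.
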